### Clinical evaluation and follow up

At screening, parents and guardians to all children in the study area aged 4-6 years and 1-2 years will be targeted for information on study participation. Those who are willing and sign the informed consent will undergo a full clinical evaluation including blood sampling for biological screen. Among those emerging as healthy, 45 children fulfilling the study inclusion criteria and who do not have any exclusion criteria, will be selected randomly and invited to participate in the study. The detailed information on this process is provided in the SOP on enrolment of participants.

On every vaccination visits, children will undergo a full physical examination before receiving the injection. Following each injection, they will be observed for one hour to assess for any adverse events following immunisation before they can return to their home. They will further be visited daily at home to evaluate for solicited local and systemic reactions for five days. The final evaluation (day 6) will be done at the clinic.

### Safety monitoring plan

This trial is overseen by a Data Safety Monitoring Board (DSMB), operating under a charter.

The DSMB will be notified of all SAEs within 24 hours. In addition there are defined points during the trial at which cumulative safety data will be reviewed by the DSMB.

The PI, the LSM, and DSMB are empowered to suspend the trial for any safety concern. To supplement this, the protocol defines criteria for the suspension of vaccination.

### Data Safety Monitoring Board (DSMB)

The DSMB for this study is a four member group of skilled professionals constituted according to AMANET procedures that respect international standards. These experts will monitor the progress of the study with particular interest in the safety of trial participants. Their composition, mandate and terms of reference are provided in the annexed DSMB charter.

Briefly, in this study, the DSMB will be responsible for:

- On going safety review and follow up in a unblinded manner
- Receive and review SAE’s when they occur
- Make recommendations to AMANET on the safety balance between the two comparison groups; and
- Make recommendations regarding continuing, amending or termination of the study for safety reasons.

The DSMB will receive progress reports one week after each injection within the first four months. SAE’s will be notified to the chair of the DSMB within 24 hours of the investigator learning of them.

The DSMB must be informed by AMANET as sponsor of the following safety data on an ‘as received’ basis:

- All SAEs;
- All withdrawals of study subjects by the Principal Investigator or the parent(s)/guardian(s) of a subject due to adverse events.

The DSMB will receive from the sponsor, AMANET:

- New information that may affect adversely the safety of the subjects or the conduct of the study;
- All subsequent protocol amendments, ICF changes or revisions of other documents originally submitted for review;
- All subsequent protocol modifications (for information).

The DSMB is empowered to suspend the enrollment to the trial and/or vaccination on the trial pending review of potential safety issues;

### Local Safety Monitor (LSM)

The overall role of the Local Safety Monitor (LSM), who is an experienced clinician based in Ouagadougou, will be to support the clinical investigators and to act as a link between the investigators and the DSMB.

The LSM’s role will include:

- Acting as the study volunteer’s advocate;
- Promptly communicating relevant safety information to the DSMB;
- Providing advice to the investigators on whether a set of clinical circumstances in a study warrants formal notification to the DSMB;
- Unblinding a subject if deemed necessary to allow for adequate treatment;
- Liaising closely with the chair of the DSMB throughout the course of the trial;
- Suspension of vaccination for a major safety concern pending discussion with the DSMB

### Data Reviewed by the LSM

The LSM must be informed by the investigator on an ‘as received’ basis of:

- All SAEs;
- All withdrawals of study subjects by the Principal Investigator or the parent(s)/ guardian(s) of a subject due to adverse events.

### Safety monitoring reports

In each group after all the subjects have completed the 7 days of follow up, a safety report will be produced for the DSMB. In total, 5 safety reports will be provided to the DSMB. An independent statistician will analyze the data and prepare an unblinded report for the DSMB thereby maintaining the blind of the study staff. If a criterion for the suspension of progression of the study is met, or the DSMB have any safety concerns about the vaccines, they may suspend the progression to the next sequential vaccine dose or to the next dose level. The process outlined in Sections 5.2.11 will be followed.

The reports will contain for each group:

- All SAEs and any relationship to vaccine;
- In each group, for each of the first two doses (i.e. after Dose 1 and Dose 2) of MSP3 and Hepatitis B, all solicited AEs tabulated by severity grading (any and Grade 3 alone) and relationship to vaccine;
- In each group, for each of the first two doses (i.e. after Dose 1 and Dose 2) of MSP3 and Hepatitis B, all unsolicited AEs tabulated by severity grading (any and Grade 3 alone) and relationship to vaccine;
- All laboratory values up to 28 days post Dose 2 presented as number of subjects out of range (above and below normal range) at each sampling time point (post doses 1 and 2 of MSP3 and Hepatitis B) tabulated by toxicity grading scale;
- All withdrawals of study subjects by the Principal Investigator due to adverse events recorded from the children or withdrawals of children by the parent(s)/guardian(s) following doses of MSP3 and Hepatitis B (expressed as percentage of subjects enrolled).

To allow the decision making for the progression to the next cohort, a comprehensive cumulative safety report of all the data collected up to date will be submitted to the DSMB in the same format as described above.

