### Method of blinding and breaking the study blind

Data pertaining to the trial will be collected in a double blinded (observer blinded) manner. “Double blinded (observer blinded)”in this context means that the vaccine recipient and their parent(s)/guardian(s) as well as those responsible for the evaluation of safety and immunogenicity endpoints will all be unaware the exact treatment, (MSP3 or Hepatitis B)given to the participant. The only study staff aware of the vaccine assignment for Hepatitis B or MSP3 will be those responsible for the storage and preparation of vaccines; these staff will play no other role in the study.

. Sealed envelopes labelled with the study ID number and containing the treatment allocated to each particular ID number will be provided to the investigator. The clinical investigator will only be allowed to open an envelope after ensuring that the child before him has met all eligibility criteria and has been given the study ID number. For each child, eligibility will have to be counter checked and signed by a second person before allocation of study ID number.

All envelopes will be retained to be checked by the clinical monitor.

The local safety monitor who is independent from the study team will also be provided a sealed randomisation list corresponding to each group. In total, 2 sealed randomisation list will be provided. If deemed necessary for reasons such as safety, the Local Safety Monitor in Ouagadougou as well as AMANET Central Safety will unblind the specific enrolled subject without revealing the study blind to the investigators.

As part of the safety monitoring plan, safety reports will be produced at 5 timepoints in the trial. An independent statistician will analyze the data, thereby maintaining the blind of the investigator group.

A formal reporting and analysis plan (RAP) will be developed. Once the study is completed and the database locked. AMANET will be responsible for initiating the execution of the statistical analysis plan in collaboration with the investigator team and breaking the blind.

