### Vaccination and serological schedule

Scheduled clinic visits are planned at day -28, 0, 6, 28, 36, 56, 63, 84, 168 and 365. Three vaccine doses will be administered by subcutaneous injection (day 0, 28 and 56). As shown in the flow chart (see page 9), participants will be monitored for the hour following vaccination, then a field worker will visit them at home on each of the 5 days following the injection. The patient will come back to the clinic at the 6th day following each immunization to be assess by a study clinician. Six serological blood sampling points have been planned on days 0, 28, 56, 84, 168 and 365.

Biological evaluations will also be done on days -28, 0, 6, 28, 36, 56, 63, 84 and 365. Apart from these standard examinations, other tests may be performed if deemed necessary.

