# Primary evaluation criteria

## Definition of the Criterion

The reactogenicity and the safety shall be assessed on the following criteria:

1. Immediate reactogenicity (within 60 minutes, with emphasis on allergic reactions),
2. Local and systemic reactogenicity during the 7 days following each vaccination.
3. Any unsolicited adverse events (AE) occurring outside scheduled visit times, up to one month after the third vaccine dose and requiring a physician visit
4. Any serious adverse events (SAE) whenever they occur during the trial period (from first visit to last visit). The relationship with the vaccine must be determined by the investigator, using the following definitions: **not related, possibly related, probably related, definitely related.**
5. Biological safety, assessed four weeks after each injection, in relation to the baseline data profile on the following:

RBC, haemoglobin, haematocrit, platelets, WBC, Liver enzymes (SGOT, GPT, total bilirubin) and creatinine.

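### The DSMB report content in section 5.2.10 stops at dose 2, so it omits group 1's non-serious third-dose data before group 2's third 30 µg dose; section 6.3 also calls the DSMB reports blinded

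*Protocol*

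**What the plan says.** Section 5.2.10 calls for a safety report in each group once all its subjects have completed 7 days of follow-up. It then lists the content:

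- Solicited events: "for each of the first two doses (i.e. after Dose 1 and Dose 2) of MSP3 and Hepatitis B, all solicited AEs", by severity and relationship. The line for unsolicited events carries the same two-dose limit.
- Laboratory data: "All laboratory values up to 28 days post Dose 2 presented as number of subjects out of range".
- Serious adverse events, and withdrawals by the investigator or parents: no dose limit.

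On number, the section states "In total, 5 safety reports will be provided to the DSMB", and section 5.2.2 agrees ("safety reports will be produced at 5 timepoints in the trial"). Neither says which group and dose each report follows. For progression to the next cohort, section 5.2.10 adds that "a comprehensive cumulative safety report of all the data collected up to date will be submitted to the DSMB in the same format" as the listed reports.

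Section 5.2.7 has a further commitment: "The DSMB will receive progress reports one week after each injection within the first four months". It does not say what those progress reports contain.

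On blinding, section 5.2.7 has the DSMB review safety unblinded, and section 5.2.10 has an independent statistician prepare an unblinded report so that study staff stay blind. Section 6.3 says that the regular reports compiled for the DSMB are to be blinded.

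**The concern.** The two groups are staggered by two weeks so that the lower dose runs ahead of the higher one. At the third dose that lead is useful only if the DSMB sees group 1's results before group 2 is injected. Section 5.2.10 lets the DSMB suspend the next dose for any safety concern, and that judgement should rest on the latest data. As written, the AE tables and the laboratory listing stop one dose short.

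The third dose matters for a reason given in the protocol's own account of the adult trials. In the Swiss trial, with 30 µg in aluminium hydroxide, the increase in local reactions appeared only after the third dose. Non-serious local reactions are what the solicited tables would capture, and what the serious-event and withdrawal lines would mostly miss. The rationale section adds that all earlier experience with this vaccine was in adults, so group 1's third dose is the first third-dose experience in children.

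The blinding conflict is separate. Two sections describe unblinded review and one describes blinded reports.

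**Working it through.** **Inputs.** Vaccination days are 0, 28, 56 (group 1) and 14, 42, 70 (group 2), from section 3. Solicited follow-up is the vaccination day plus 6 days (section 3). Laboratory days come from section 5.2.4: "Biological evaluations will also be done on days -28, 0, 6, 28, 36, 56, 63, 84 and 365". Group 1 has 15 children on 15 µg and 8 on hepatitis B (section 3). Anticipated loss or deviation is at most 10% (section 16.2).

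**The stated number of reports.** Two groups times three doses gives six 7-day follow-up endpoints: days 6, 34, 62 for group 1 and days 20, 48, 76 for group 2. The vaccinations that follow them are on days 14, 42 and 70 for group 1's endpoints, and on days 28 and 56 for group 2's first two. Nothing follows day 76. Five endpoints therefore precede a later vaccination, which reproduces the stated five and makes group 1 dose 3 one of them. The protocol does not confirm this reading. Four reports (two groups times doses 1 and 2) plus the cumulative report also make five. On the first reading, the report after group 1 dose 3 omits the AE tables for the dose just given. On the second, no section 5.2.10 report follows that dose.

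**Time available before group 2's third dose.**

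- End of group 1 dose 3 follow-up: 56 + 6 = day 62, so 70 − 62 = 8 days.
- Group 1 clinic and laboratory visit on day 63: 70 − 63 = 7 days.
- Assumption: the visit windows mean ±4 days (the sign is lost in the text) and apply to each group independently. Group 1 dose 3 then falls on days 52–60, follow-up ends on days 58–66, the visit falls on days 59–67, and group 2 dose 3 falls on days 66–74. The gap from end of follow-up runs from 66 − 66 = 0 to 74 − 58 = 16 days. The gap from the visit runs from 66 − 67 = −1 to 74 − 59 = 15 days.

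**What the listed content leaves out at that point.**

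- Complete 7-day solicited data on 15 + 8 = 23 children, or 0.9 × 23 = 20.7 (about 21) after 10% loss.
- The first 7 (day 62) or 8 (day 63) of 28 days of unsolicited events.
- One of five post-vaccination laboratory points. The listed cut is 28 + 28 = day 56, so days 6, 28, 36 and 56 are covered and day 63 is not.

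**What could not be available in any case.** Section 14.1 defines "Biological safety, assessed four weeks after each injection". For group 1 dose 3 that is 56 + 28 = day 84, after day 70. The final analysis one month after dose 3 is also too late.

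**Clinical signal.** The Swiss finding concerns local reactions in unexposed adults. In exposed adults in Burkina Faso, the MSP3 arm changed little from dose 2 to dose 3: pain 5 to 5, swelling 8 to 7, induration 2 to 3, each of 15.

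**Blinding.** Section 6.3 (blinded reports to the DSMB) cannot be true together with section 5.2.10 (unblinded report) and section 5.2.7 (unblinded review) if all three concern the same reports. Nothing in the text separates them.

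**The case against.** The strongest reply is that the DSMB has other routes to the data. Section 5.2.7's one-week progress report after group 1 dose 3 falls at about day 63, before day 70. Its content may be set in the annexed DSMB charter or in the SOP on interim and final reports, neither of which is shown. Serious events and AE withdrawals go to the DSMB and the local safety monitor as they occur. The investigator, the local safety monitor and the DSMB can each suspend vaccination. Both 30 µg doses already given to group 2 are tabulated, and the missing data come from a lower dose. On blinding, the only section that instructs the statistician is 5.2.10, and it is clear.

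Most of this stands and limits the point. It does not remove it. The protocol is not silent on content: it states a two-dose limit, and a charter asking for more would contradict it. The cumulative report does not settle the matter either, because it is tied to the next cohort and keeps the same format.

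A reader might infer more than the text supports:

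- That third-dose oversight is lost. It is not, for the reasons above.
- That five reports contradict section 5.2.7's six (two groups times three injections). This is an ambiguity, since the progress reports may be a separate stream.
- That section 16.2's 80%, 90% and 95% detection probabilities measure the gap. They concern systemic reactions or serious adverse events, whereas the adult signal is local, and they do not show that a DSMB decision would change.
- That section 6.3 gives the independent statistician an opposite instruction. It does not mention that role.
- That the denominators for withdrawals (enrolled in 5.2.10, vaccinated in 5.2.11) are an error. Randomisation is at first vaccination, so they should nearly coincide.

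**Conclusion.** The point holds in a limited form. The content list in section 5.2.10 is cut at the wrong place: it excludes the non-serious third-dose results of up to 23 children, available a nominal 7 to 8 days before group 2's third 30 µg dose. What is affected is the DSMB's discretionary review before that dose. The section 5.2.11 triggers, which rest on serious events, anaphylaxis and withdrawals, are not affected.

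The 7 to 8 days rest on the provisional calendar. The stagger may be extended, and under the assumed ±4-day windows the time could shrink to nothing. The clinical reason is indirect, from adults, and the two adult trials point in different directions. Whether the DSMB would in practice lack the tables cannot be settled without the charter.

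The conflict between section 6.3 and sections 5.2.7 and 5.2.10 is a plain contradiction. The likely intent is the unblinded report. Both items deserve correction because the remedy is cheap, not because the trial is unsafe as designed.

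**What to change.** 1. In section 5.2.10, make both AE lines cover every dose given up to the data cut, in place of the limit to the first two doses.
2. In the laboratory line, ask for all values available at the data cut, which brings in day 63 for group 1.
3. State that a report with this content follows group 1 dose 3 and reaches the DSMB before group 2 dose 3. If visit windows use up the interval, hold group 2's third dose until the report has been received; section 3 already allows the stagger to be extended for safety concerns.
4. Keep section 5.2.7's one-week report after every injection, including group 2 dose 3. Deferring that dose to the final analysis would remove oversight already promised.
5. In section 6.3, delete the sentence on blinding of the DSMB reports, or limit it to the study team.

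The cost is wording in two sections and slightly more tabulation. No visit, sample or child is added.

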### Process for the suspension of progression to the next sequential vaccine dose or to the dose escalation

Suspension of the next sequential vaccine dose or dose escalation, pending full review of available data by the DSMB will take place if:

- The Principal Investigator suspends vaccination for any of the following SAEs pending review by the DSMB;
- Death or life-threatening SAE which is judged to be related to the study vaccine;
- Anaphylactic shock reaction in an enrolled subject following vaccination.
- The DSMB recommend suspension of all vaccination for any one SAE or pattern of SAEs. The DSMB will communicate their recommendation to the Principal Investigator who will enact it. The DSMB will notify the sponsors of their decision immediately;
- A safety report shows > 5% of subjects vaccinated with MSP3 or Hepatitis B are withdrawn by the investigator for local or systemic reactogenicity in recipients;
- In making their recommendation the DSMB will take into account the full clinical history of each withdrawn child.

### Process if the trial is suspended on the basis of safety reports

If the trial is suspended, the DSMB will review all available information (which will include the experience of all children to have been vaccinated) and make a recommendation to the study sponsor (AMANET) whether to recommence the trial and proceed to the next vaccination (sequential vaccine dose, or to dose escalation or to the next cohort) or to stop the trial permanently.

Although the trial may be suspended by the DSMB, the LSM or the Principal Investigator, it is the responsibility of the sponsor (AMANET) to make the final recommendation whether or not the trial should be stopped permanently.

## Termination of the trial

AMANET as the trial sponsor reserves the right to terminate this study. The trial may be discontinued for the following reasons:

1. If new data about the investigational product resulting from this or any other trials become available that dictates that the product is not safe for human use;
2. When AMANET so advises based on administrative reasons or other advices from the DSMB;
3. When the National Ethics Committee so decides.

If a trial is to be prematurely terminated or suspended, AMANET shall promptly inform the investigators, the Regulatory Authorities and the Ethics Committee of the reason for termination.

Should the principal investigator deem termination inevitable, he may suspend study activities while immediately resolving the issues raised with AMANET.

# Data collection and handling

## Source data

All records bearing participant information which is generated during this study shall constitute primary or source documents. This includes the files opened for the participants as record files, hospital files, study log books, dairy cards, and hospital files in case of hospitalisation. All laboratory result sheets will also be considered as source documents. A list of agreed source documents will be maintained in the investigator file, and these shall be used for verifying entries on CRF by the monitor.

The investigator shall make every effort to ensure that these documents are maintained and safely kept as advised by the sponsor considering relevant regulatory requirements.

## Case Report Forms

The CRF constitute important study documentation and will be written on “no carbon required” triple copy paper (white, yellow and pink). Only investigator team officers dully authorised will be allowed to write on CRF and a copy of authorised signatories will be maintained in the study file.

Some of the information, especially participant personal socio-demographic details may be entered directly onto CRF. However, most of the information will be transcribed from source data which will be retained for monitor verification and audit trail. The Principal Investigator takes total responsibility to ensure that correct information is entered on the CRF and shall sign on each CRF to this effect.

Entries shall be made with a black ball point pen. Any corrections made must remain legible, and should only be a neat crossing line, date and initials of the authorised person making the correction and the new entry besides it.

After monitor verification, the original CRF page (white) will be withdrawn and sent to the data management; the yellow page will be shipped to AMANET and the pink page will remain to be stored with the investigator at site together with other essential study documents.

